## Methods/design

### Study design

The study protocol was approved by the Medical Ethics Committee of Longhua Hospital Affiliated to Shanghai University of Traditional Chinese Medicine (2017LCSY069) and registered in the Chinese Clinical Trial Registry (http://www.chictr.org.cn/edit.aspx?pid=24555&htm=4) with number ChiCTR1800014364 on 1 January 2018.

This study will be a 16-week, randomized, multi-center, double-blinded, three-arm, dose-optimization, placebo-controlled clinical trial. A total of 243 patients with NAFLD will be recruited through recruitment advertisements and introductions from doctors from three community healthcare centers in Shanghai, namely Zhangjiang community healthcare center, Beicai community healthcare center, and Sanlin community healthcare center. All three centers are based in Pudong New Area, Shanghai and no obvious difference will be supposed to exist in population and socioeconomic aspects. Eligible patients with NAFLD who agree to participate in the study will be randomly assigned to the standard dose Lingguizhugan decoction (SLGD) group, low dose Lingguizhugan decoction (LLGD) group, or the control group on a ratio of 1:1:1. On the basis of behavioral intervention therapy, patients in the SLGD and LLGD groups will be treated with different doses of LGZG; the control group will receive placebo. The LLGD group will be made of half of the standard dose, and the placebo will be one-tenth of the standard dose but with soluble starch, mixed colorant, and bitter component to achieve a comparable appearance, smell, and taste. The course of treatment will last 12 weeks. A 4-week follow-up will also be arranged to assess the continued effect. Participants will be assessed at week 0 (baseline), week 4, week 8, week 12 (end of treatment), and week 16 (end of follow-up). All participants will be asked to provide written informed consent before entering the trial. The study flow chart is shown in Fig. 1 and participant timeline is presented in Table 1. The Standard Protocol Items: Recommendations for Interventional Trials (SPIRIT) Checklist is presented in Additional file 1.

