#### Behavioral intervention

Behavioral interventions will be given to all three groups and the prescription will be based on the Guidelines for Prevention and Control of Overweight and Obesity in Chinese Adults [32]. In brief, participants will be required to limit calorie intake (approximate 1660 kcal per day) and guarantee physical exercises (moderate aerobic exercise at least 150 min per week). Individuals will be asked to complete daily dietary and exercise records during treatment (Additional file 2).

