#### Drug intervention

LGZG is a traditional formula which is composed of *Poria* (Fulin), *Ramulus Cinnamomi* (Guizhi), *Rhizoma Atractylodis Macrocephalae* (Baizhu), and *Radix Glycyrrhizae* (Gancao). The standard dose for each herb is 12 g, 9 g, 6 g, and 6 g, respectively. The LLGD group will be made of half of the standard dose and the placebo will be one-tenth of the standard dose. The course of treatment lasts 12 weeks. Participants will be required to take one dosage (one pack) of granules 30 min after breakfast, once daily on weekdays. A total of 60 packs per patient will be administrated. The granules used in this study will be produced by Sichuan Neo-green Pharmaceutical Technology Development Co., Ltd. (Sichuan, China). The crude herbs will be extracted and made into granules. The production process will be under the standard of Good Manufacturing Practice. No significant difference was found among granules samples from the three groups in terms of color, appearance, shape, smell, and weight (Fig. 2).

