### Outcome measures

The schedule for all outcome measures is shown in Table 1. All demographic data will be determined before treatment, including the date of birth, gender, body weight, height, medication history, past medical history, smoking and drinking status, and course of disease.

The primary outcome will be the proportion of participants with at least a 1-unit decrease of HOMA-IR from baseline to treatment endpoint (week 12) [33]. Secondary outcomes will include body measurements (body weight and body mass index), hepatic function (alanine aminotransferase [ALT], aspartate transaminase [AST], gamma-glutamyl transpeptidase [GGT], and alkaline phosphatase [ALP]), lipid metabolism profiles (total cholesterol [TC], TG, low-density lipoprotein cholesterol [LDL-C], high-density lipoprotein cholesterol [HDL-C], apolipoprotein A [apoA], apolipoprotein B [apoB], and non-high-density lipoprotein cholesterol [non-HDL-C]), glucose metabolism profiles (fasting blood glucose [FPG], fasting insulin [FINS], and glycosylated hemoglobin [HbA1c]), inflammatory responses (white blood cell [WBC] counts, C-reactive protein [CRP], and inflammatory cytokines), liver-kidney echo ratio by ultrasound, and scorings of various questionnaires (TCM spleen-yang pattern scale, the MOS item short from health survey [SF-36], self-rating depressive scale [SDS], and self-rating anxiety scale [SAS]). All secondary outcomes will also be evaluated from baseline to treatment endpoint.

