### Statistical analysis

The analysis of efficacy and safety will be based on the principle of intention-to-treat (ITT), namely all randomized participants will enter the final analysis. The missing value will be filled by the method of the last observation carried forward. Data will be presented as mean with standard deviation, median with range, or number with percentage. Data analysis will use the SPSS 19.0 for Window software. All statistical inferences will be performed using a two-sided test with a statistically significant test level of *P* < 0.05 and the confidence interval of parameters will be estimated by 95% confidence interval. Differences within groups will be assessed by paired t-test, chi-square test, or Wilcoxon signed rank test according to specific variables. Differences between groups will be assessed by one-way analysis of variance or Kruskal–Wallis test based on characteristics of data. Post-hoc pairwise multiple comparisons will be performed if statistical significance is found.

No interim analysis was arranged in this trial due to a short intervention period and safety profiles of LGZG. Potential sub-group analyses will be determined based on characteristics of included participants, for instance, different categories of body mass index and different combined diseases.

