## Discussion

NAFLD is a widely health problem and > 80% of obese people suffer from NAFLD globally [36]. A large population-based study has demonstrated that NAFLD is one of the important causes of hepatocellular carcinoma (HCC) and the incidence of NAFLD-related HCC is increasing by approximately 10% per year [37]. However, the pathogenesis mechanism of NAFLD is vague [38]. There is still no drug currently approved for the treatment of NAFLD by the U.S. Food and Drug Administration (FDA) or the European Medicines Evaluation Agency (EMEA) [10, 39]. Hence, many patients with NAFLD will seek help from TCM interventions, especially Chinese herbal medicine.

Treatment based on pattern differentiation is the character of understanding and treating disease by TCM. Therefore, we introduce pattern differentiation as one of inclusion criteria for NAFLD participants, namely spleen-yang deficiency. LGZG is the corresponding formula for this pattern. Previous animal studies also indicated the potential efficacy of LGZG against NAFLD [20, 22]. A clinical trial will then be necessary to demonstrate the application. To our knowledge, our trial is the first multi-center, randomized, double-blinded, placebo-controlled clinical trial to assess the efficacy and safety of LGZG for NAFLD.

To ensure the quality of this research, a strict system of training and supervision will be established. Training sessions will be held for each center to explain the study protocol and potential upcoming matters. How to confirm the TCM pattern of spleen-yang deficiency and how to collect biological samples will also be explained in training sessions. The biochemical measurements of each participating center will be tested uniformly by KingMed Diagnositics (Shanghai) to guarantee the consistency. The ECG and liver-kidney echo ratio by ultrasound will be examined in the corresponding experimental center with uniform standard.

The results of this trial will provide initial evidence regarding the efficacy and safety of LGZG in the treatment of NAFLD with spleen-yang deficiency pattern. Biological samples collected in this trial may explain the possible action mechanisms of LGZG associated with oral and gut microbiota.

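### Continuous secondary outcomes are compared without baseline adjustment, and the added within-arm before-after tests do not estimate the effect of LGZG against control

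*Protocol article*

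**What the plan says.** The Statistical analysis section of the protocol article names the between-arm methods: "Differences between groups will be assessed by one-way analysis of variance or Kruskal–Wallis test based on characteristics of data". It adds that "Post-hoc pairwise multiple comparisons will be performed if statistical significance is found". For change inside each arm it states: "Differences within groups will be assessed by paired t-test, chi-square test, or Wilcoxon signed rank test according to specific variables". No model with a covariate is named.

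On the scale of analysis, Outcome measures says: "All secondary outcomes will also be evaluated from baseline to treatment endpoint". The abstract likewise describes the secondary outcomes as changes. The likely reading is that change scores enter the ANOVA, but the Statistical analysis section does not say so. Table 1 schedules a week-0 measurement of these outcomes.

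Three other statements bear on the point. Under Behavioral intervention: "Behavioral interventions will be given to all three groups", with a limit near 1660 kcal a day and at least 150 minutes of exercise a week. Under Diagnostic criteria, entry requires a pattern score of at least 20, and that scale is also a secondary outcome. The Discussion says that biochemistry goes to one laboratory, whereas the "liver-kidney echo ratio by ultrasound will be examined in the corresponding experimental center with uniform standard".

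**The concern.** There are two separate matters.

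1. **Precision.** One-way ANOVA and Kruskal–Wallis take no covariate. This is a stated method and not a detail left to an analysis plan, because a plan could add adjustment only by departing from the published text. The baseline is already measured, so leaving it out of the model gives wider intervals than the same data allow.

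2. **Within-arm tests.** A before-after P value in one arm mixes any herb effect with everything else that changes over 12 weeks. Here that includes a lifestyle programme shared by all arms and, for the pattern scale, regression to the mean after selection on a high score. Such a test does not estimate LGZG against control. If a report set a significant active arm beside a non-significant placebo arm, readers could take the contrast for evidence of efficacy when the arms do not differ.

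**Working it through.** The article gives no figure for the secondary outcomes that could be reproduced. The inputs are as follows.

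- From Sample size estimation: 81 per arm, 20% dropout (81 × 0.8 ≈ 65 completers).
- From Statistical analysis: two-sided tests at 0.05.
- Assumed: correlation r between baseline and week 12, equal SD σ at both times, and a common shift d in units of σ.

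**Precision of the between-arm comparison**

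Per-patient variances are σ² for week-12 values, 2σ²(1−r) for change and σ²(1−r²) for ANCOVA. Hence:

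- ANCOVA / change = (1−r²)/(2−2r) = (1+r)/2
- ANCOVA / week-12 = 1−r²

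| r | ANCOVA / change | ANCOVA / week-12 |
|---|---|---|
| 0.3 | 0.65 | 0.91 |
| 0.5 | 0.75 | 0.75 |
| 0.7 | 0.85 | 0.51 |
| 0.8 | 0.90 | 0.36 |

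Interval width scales with the square root. Against change scores, √0.75 = 0.87 and √0.90 = 0.95, so intervals are about 13% narrower at r = 0.5 and 5% narrower at r = 0.8. In patients, 1/0.75 = 1.33 and 1/0.90 = 1.11, which equals 11–33% more patients. Against week-12 values, √0.75 = 0.87 and √0.36 = 0.60, so intervals are 13–40% narrower.

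In terms of power, take a pairwise difference of 0.44 SD, which has 80% power on week-12 values with 81 per arm:

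| r | Change scores | ANCOVA |
|---|---|---|
| 0.3 | 65.8% | 83.6% |
| 0.5 | 80.0% | 89.9% |
| 0.7 | 95.1% | 97.5% |

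**Within-arm tests when the arms do not differ**

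Give all three arms the same shift d. The paired t-test has noncentrality d√n/√(2−2r). Let p be its power in one arm. Then:

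- P(all three arms significant) = p³
- P(at least one active arm significant, placebo not) = (1−p)[1−(1−p)²]

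Example with n = 81, r = 0.5, d = 0.3: noncentrality 0.3 × 9/1 = 2.7 and p = 0.76. Then p³ = 0.44, and 0.24 × (1 − 0.24²) = 0.23.

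| d (n = 81) | One arm, r = 0.5 | All three, r = 0.5 | Active yes, placebo no, r = 0.5 | All three, r = 0.7 | Active yes, placebo no, r = 0.7 |
|---|---|---|---|---|---|
| 0.1 | 0.14 | 0.003 | 0.23 | 0.01 | 0.30 |
| 0.2 | 0.43 | 0.08 | 0.39 | 0.25 | 0.32 |
| 0.3 | 0.76 | 0.44 | 0.23 | 0.81 | 0.07 |
| 0.4 | 0.95 | 0.84 | 0.06 | 0.99 | 0.004 |
| 0.5 | 0.99 | 0.98 | 0.01 | >0.99 | <0.001 |

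With 65 completers and r = 0.5 the picture is similar: the last pattern has probability 0.20 at d = 0.1 and 0.38 at d = 0.2. Small common shifts tend to give discordant significance, and larger ones give significance everywhere. Neither pattern says anything about the herb, because the arms were set equal.

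**The case against.** The strongest defence is that nothing here is invalid. Unadjusted tests on randomised arms keep their type I error, and that error rate already allows for chance baseline imbalance. If change scores are analysed, as the text suggests, the baseline is already used, and the remaining gain is modest and rests on assumed correlations. Only secondary outcomes are touched. All of this stands, and it limits the point to efficiency and interpretation.

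Four stronger readings are tempting but unsupported:

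- **Every arm will show improvement.** The article gives no size for the lifestyle effect. At a 0.2 SD shift, all three arms are significant with probability only 0.08 to 0.25.
- **Efficacy will be judged from within-arm P values.** The text does not say so. Direct between-arm tests, with pairwise comparisons after a significant result, are planned alongside.
- **Regression to the mean affects all secondary outcomes.** The threshold of 20 applies to the pattern scale. The eligibility criteria set no cut-off on weight, BMI, liver enzymes, lipids, SF-36, SAS or SDS.
- **Centre differences spoil the comparison.** The article quantifies no centre effect, uses one laboratory for biochemistry and calls for a uniform ultrasound standard. A constant additive offset in reading the echo ratio cancels in a change score.

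The defence does not remove the main point: the named tests exclude a covariate that is already collected, and the within-arm tests answer a question that the trial does not ask.

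**Conclusion.** The point holds as a recommended improvement to the secondary analyses, and not as a validity failure. Against change scores, the likely reading, ANCOVA saves 10–25% of variance at r = 0.5 to 0.8. It saves 25–64% if week-12 values alone are compared. These figures assume equal SDs at the two times and a correlation that the article does not give.

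The within-arm tests carry a real risk of misreading. With no difference between arms and a common shift of 0.1 to 0.2 SD, an active arm is significant and placebo is not with probability 0.23 to 0.39 (n = 81, r = 0.5 or 0.7). How far this occurs depends on the unknown common shift. The primary outcome and the sample size are unaffected.

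**What to change.** 1. Analyse each continuous secondary outcome by ANCOVA of the week-12 value, log-transformed where skewed, on arm and its own baseline. Report adjusted between-arm differences with 95% confidence intervals.
2. For the locally read echo ratio, a centre term is optional but sensible. When the baseline slope is below 1, ANCOVA removes only part of a constant centre offset.
3. Drop hypothesis tests of change within arms and give within-arm change as description only.

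No new data are needed. The cost is one degree of freedom for baseline and two for three centres, plus a documented change. Trial status says that the data were locked in June 2019, and the article does not say whether the codes have been opened. The change should be dated before the first of the two unblinding steps described under Randomization and blinding. If unblinding has passed, the ANCOVA should be reported as a labelled additional analysis beside the published method.

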### Participants

#### Diagnostic criteria

All participants should meet the diagnostic criteria of NAFLD and TCM pattern differentiation criteria of spleen-yang deficiency. Diagnostic criteria of NAFLD will be based on the American Association for the Study of Liver Diseases (AASLD) in 2017 [12]. To be specific, the following four criteria should all be met: (a) imaging (ultrasound, computed tomography, or magnetic resonance imaging) or histological evidence of hepatic steatosis; (b) no significant alcohol consumption, defined as > 21 standard drinks per week in men and > 14 standard drinks per week in women; (c) exclusion of other reasons inducing hepatic steatosis, including but not limited to hepatitis C, specific drugs induced, parenteral nutrition, and severe malnutrition; and (d) no coexistence of other chronic liver disease, including but not limited to hemochromatosis, autoimmune liver disease, chronic viral hepatitis, alpha-1 antitrypsin deficiency, hepatolenticular degeneration, and drug-induced liver disease.

The TCM pattern differentiation criteria of spleen-yang deficiency will refer to the expert consensus of spleen deficiency by China Association of Traditional Chinese Medicine in 2017, previous systematic review, and the clinical guidelines for the new Chinese medicine [29–31]. Ten symptoms and signs will be assessed by continuous 100-point scale, a higher score means a more severe degree. Every symptom or sign possesses with a certain weight. The scoring will be calculated through multiplying the rating score by the weight. Spleen-yang deficiency pattern will be defined as total score of 10 dimensions ≥ 20. The detailed rating scale is shown in Table 2.

**Table 2 Tab2:** Spleen-yang deficiency pattern scale

Symptoms	Score (0–100)
Do you feel too lazy to speak?	20%
Do you sweat often or have night sweats even though you are not active and it is not hot?	5%
Do you have bland and tasteless feeling in your mouth?	10%
Does your stool have a thin texture and is loose?	20%
Do you feel more saliva?	10%
Do you have bleeding gums?	5%
Do you feel a lack of warmth in the extremities	10%
Do you have insomnia/trouble sleeping at night?	5%
Are you likely to catch a cold?	10%
Do these symptoms affect your eating habits (such as hate greasy good)?	5%
Total	

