Safety variables will include vital signs (including blood pressure, respiratory, heart rate, and body temperature) evaluated at every visit, electrocardiogram (ECG) and blood tests (including blood routine test and renal function) evaluated at baseline, week 4, and week 12. Adverse events (AEs) will be observed and recorded throughout the whole trial. LGZG is a classical herbal formula and has satisfactory safety profiles. Potential AEs may be mild gastrointestinal reactions, which will be alleviated spontaneously without any additional medical interventions. Clinical investigators should document any AEs in a case report form (CRF), including the following information: occurrence time; symptoms and signs; severity; duration; laboratory examinations; interventions; outcomes; and follow-up time. If an AE occurs, clinical investigators should adopt appropriate measures to guarantee the safety of participants based on the actual situation. If serious AEs occur, clinical investigators should inform the principal investigator within 2 h of the event. The principal investigator should then report to the Medical Ethics Committee and Data Monitoring Committee (DMC) within 24 h. It will be decided whether to terminate the trial after a discussion.

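### The within-group sentence names an unqualified chi-square test for same-patient comparisons; taken literally it ignores the pairing, though the impact is minor

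*Protocol article*

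**What the plan says.** Protocol article, Statistical analysis, on changes within an arm: "Differences within groups will be assessed by paired t-test, chi-square test, or Wilcoxon signed rank test according to specific variables".

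The next sentence covers comparisons between arms: "Differences between groups will be assessed by one-way analysis of variance or Kruskal–Wallis test based on characteristics of data". The chi-square test therefore appears only in the within-group sentence.

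The same patients are seen at weeks 0, 4, 8, 12 and 16 (Study design). Among the safety variables, Outcome measures lists "electrocardiogram (ECG) and blood tests (including blood routine test and renal function) evaluated at baseline, week 4, and week 12". It does not say whether these are analysed as values or as normal/abnormal categories.

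The primary outcome is binary and is already built from change: "proportion of participants with at least a 1-unit decrease of HOMA-IR from baseline to treatment endpoint (week 12". It has no baseline value of its own to pair with. The secondary outcomes are laboratory values, body measurements, the echo ratio and scale scores; none is defined as a category.

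**The concern.** The sentence picks the matched method for continuous data (paired t-test) and for ranked data (signed rank), then gives categorical data a name that ordinarily means the test for independent groups. Two readings on a given patient are not independent.

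If the test is run on the baseline and later proportions as though they came from two separate samples, its standard error omits the covariance between visits. Positive correlation, the usual case, makes that standard error too large, so real change is harder to detect. For safety data this is the unwelcome direction: a genuine rise in abnormal ECGs or laboratory results within an arm is more easily passed over.

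This is a method that the text names, not detail that the text leaves out.

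**Working it through.** The plan gives no figure on this point to reproduce. The check asks how a Pearson chi-square behaves on paired binary data at the plan's group size.

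**Inputs**
- From the protocol: two-sided 5% level (Statistical analysis); 81 patients per group and at most 20% dropout, so 81 × 0.8 ≈ 65 completers (Sample size estimation). The 81 is used only as a group size and is not examined here.
- Assumed, because the protocol gives none: 30% abnormal at both visits when nothing changes; 18% against 30% when there is change; within-patient correlation phi of 0.3, 0.5 and 0.7.

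**Type I error in closed form.** With the same proportion p at both visits, the true variance of the difference is 2p(1−p)(1−phi)/n. Pearson's test uses 2p(1−p)/n. The actual two-sided error is therefore about 2 × [1 − Φ(1.96/√(1−phi))]:
- phi 0: 1.96, giving 5.0%
- phi 0.3: 1.96/0.837 = 2.34, giving 1.9%
- phi 0.5: 1.96/0.707 = 2.77, giving 0.56%
- phi 0.7: 1.96/0.548 = 3.58, giving 0.03%

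**Joint probabilities for the change scenario.** P(abnormal at both visits) = p0·p1 + phi·√[p0(1−p0)p1(1−p1)]. For phi 0.5 this is 0.054 + 0.5 × √(0.21 × 0.1476) = 0.054 + 0.5 × 0.176 = 0.142. The discordant cells are 0.30 − 0.142 = 0.158 and 0.18 − 0.142 = 0.038. The expected number of discordant pairs is 81 × 0.196 ≈ 16; it is about 22 at phi 0.3 and 10 at phi 0.7.

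**Simulation, n = 81**

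| phi | Pearson, type I error | Pearson, power | McNemar asymptotic, power | McNemar exact, power |
|---|---|---|---|---|
| 0.3 | 2.0% | 42% | 58% | 48% |
| 0.5 | 0.6% | 40% | 72% | 63% |
| 0.7 | 0.05% | 37% | 96% | 90% |

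Power is for a 12-point change and is the same whether the proportion rises or falls. The asymptotic McNemar test keeps its type I error at about 4 to 5%; the exact version is itself conservative, at about 2 to 3%. At n = 65 the Pearson type I errors are 2.0%, 0.6% and 0.06%, so the pattern does not depend on dropout. Pearson's test is correct only at phi 0. At phi −0.2 it errs the other way (7.3% at n = 81).

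**The case against.** **McNemar's statistic is itself a chi-square.** The text says neither Pearson nor ordinary, its two neighbours are paired tests, and a condensed article may simply be naming the family. This stands as a limit on certainty. A reader might infer that the within-group P values will be wrong; the document supports only that they would be wrong if the sentence is followed literally. It does not remove the point, because the other two tests are explicitly named in paired form and this one is not.

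**There may be little to apply it to.** No before-after categorical outcome is defined. ECG and laboratory categories are possible, but their coding is not stated and the 30% rate is an assumption. This also stands. Spleen-yang pattern present or absent might look like a natural example, but it fails: the pattern is an inclusion criterion, so everyone has it at baseline, and Outcome measures treats the scale as a score.

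**False positives?** One could also run the chi-square on the before-by-after cross-table. That tests association, and at phi 0.5 gives n × phi² = 81 × 0.25 ≈ 20.3 (P about 0.000007) with no change at all. The arithmetic is right, but nothing in the text suggests that use, so it is not part of the finding.

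**The gain is smaller with the exact test.** True: at phi 0.3 the improvement is 6 points (42% to 48%), not 16. At 0.5 and 0.7 it remains large.

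**Within-arm tests do not carry the trial's conclusion.** Agreed. This is the main reason for rating the point minor.

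**Conclusion.** The point holds in a limited form. As written, the sentence gives same-patient categorical comparisons a test that, in its ordinary meaning, ignores the pairing. On the assumptions above, that test would use between 0.05% and 2.0% of its nominal 5% error, and would have 37 to 42% power where a paired test has 48 to 96%, depending on phi and on the McNemar version. The direction, over-conservative under positive correlation, needs no simulation; the sizes rest on assumed correlations and abnormality rates.

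A reader might infer that the efficacy result is compromised. The document does not support that: the primary outcome is a change-defined responder rate to be compared between arms, and this test does not analyse it. Nor does the protocol say that categorical within-group tests will be reported for ECG or laboratory safety data. The consequence is a minor error of wording that could weaken secondary within-arm statements, chiefly on safety.

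**What to change.** In the within-group sentence of Statistical analysis, replace the chi-square test with: *McNemar's test (exact when discordant pairs are few; marginal homogeneity test for more than two categories)*.

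At the same time, move the chi-square test to the between-group sentence. That sentence now lists only analysis of variance and Kruskal–Wallis, so deleting the chi-square where it stands would remove it from the plan altogether, although the primary outcome is a proportion to be compared between arms.

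The cost is an edit to two adjacent sentences. It needs no new data and no change to the design.

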### Sample size estimation

Sample size was estimated based on the clinical primary outcome. As far as we know, this is the first RCT evaluating the efficacy of LGZG versus placebo. No data are available as a reference. Therefore, based on our previous animal studies and consultation with TCM experts, we assumed that the effect size for the SLGD group is 30%, LLGD group is 15%, and placebo group is 10%. If α = 0.05 and β = 0.10, the sample size can be calculated by the following formula:
$$ \mathrm{n}=\frac{1641.4\lambda }{{\left({\sin}^{-1}\sqrt{p_{max}}-{\sin}^{-1}\sqrt{p_{min}}\right)}^2} $$

The λ is the degree of freedom, taking 12.65 in this case. The p_max_ is 30% and the p_min_ is 10%. Assuming the maximum dropout rate is 20%, 81 patients will be required for each group, with a total of 243 patients.

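### The primary outcome is a responder proportion, but the between-group tests named are ANOVA and Kruskal-Wallis, with no effect measure per dose and no adjustment for baseline HOMA-IR

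*Protocol article*

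**What the plan says.** The Outcome measures section defines a yes/no endpoint: "The primary outcome will be the proportion of participants with at least a 1-unit decrease of HOMA-IR from baseline to treatment endpoint (week 12"). The abstract says the same. The Sample size estimation section assumes rates of 30%, 15% and 10% in the standard-dose, low-dose and placebo arms, sets "If α = 0.05 and β = 0.10", and uses an arcsine formula for several proportions.

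The Statistical analysis section then divides the tests by type of comparison:

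- Between groups: "Differences between groups will be assessed by one-way analysis of variance or Kruskal–Wallis test", the choice between the two depending on the characteristics of the data.
- Within groups: "Differences within groups will be assessed by paired t-test, chi-square test, or Wilcoxon signed rank test according to specific variables".
- After a significant overall result: "Post-hoc pairwise multiple comparisons will be performed if statistical significance is found".

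The section promises 95% confidence intervals for parameters, without naming the parameter for any outcome. It bases the analysis on all randomized participants, with the last observation carried forward. Table 1 schedules HOMA-IR at week 0. Baseline HOMA-IR is not an eligibility threshold, a stratification factor or a covariate anywhere in the article.

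**The concern.** The article commits itself to two between-group methods, both meant for continuous or ordinal data. Its qualifier about the characteristics of the data only chooses between those two. The usual test for a proportion appears once, in the sentence where it does not fit. A responder is defined by change from baseline, so nobody has a responder status at baseline to pair with week 12; and truly paired binary data would call for McNemar's test.

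This is a statement that conflicts with the endpoint, not a detail left open, and an analysis plan that followed the text would inherit it. At stake is the main result of a placebo-controlled dose-finding trial: how many more participants respond on each dose than on placebo, and with what precision. An overall ANOVA or Kruskal-Wallis p-value does not give that. Baseline HOMA-IR, already measured and built into the endpoint, is also left out of the comparison.

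**Working it through.** **1. What the sample size assumes.** The plan's λ of 12.65 is the noncentrality of a 2-df chi-square test at α = 0.05 and power 0.90 (recomputed: 12.654). The trial was therefore sized for an overall comparison of three proportions. The formula with the plan's inputs gives 1641.4 × 12.65 / (33.211 − 18.435)² = 20,763.7 / 218.3 = 95.1 per group before dropout. The stated 81 after dropout is not reproduced; that is a separate matter and nothing below rests on it.

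**2. Do the named tests give a wrong p-value?** Take counts close to the planned rates: 24, 12 and 8 responders of 81 per arm (N = 243, pooled rate 44/243 = 0.1811).

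- Pearson: 81 × Σ(pᵢ − 0.1811)² / (0.1811 × 0.8189) = 81 × 0.021135 / 0.14828 = 11.545, P = 0.0031.
- Kruskal-Wallis: 11.545 × 242/243 = 11.497, P = 0.0032.
- ANOVA: F = (11.545/2) / ((243 − 11.545)/240) = 5.99, P = 0.0029.

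Simulation (40,000 runs per setting, 81 per arm) gave type I error of 0.048 to 0.051 for all three tests, and power of 0.87 for all three at 30/15/10%. With 65 per arm (81 × 0.8 = 64.8), power was 0.78 for all three.

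**3. What is missing from the result.** In the same example, with simple unpooled 95% intervals:

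| Comparison | Risk difference | Standard error | 95% interval | Odds ratio |
|---|---|---|---|---|
| Standard dose v placebo | 16/81 = 19.8 points | √(0.2963×0.7037/81 + 0.0988×0.9012/81) = 0.0606 | 7.9 to 31.6 | (24/57)/(8/73) = 3.84 |
| Low dose v placebo | 4/81 = 4.9 points | √(0.1481×0.8519/81 + 0.0988×0.9012/81) = 0.0515 | −5.2 to 15.0 | (12/69)/(8/73) = 1.59 |

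The overall P of about 0.003 conceals that the two doses look quite different against placebo.

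**4. What baseline adjustment is worth.** A participant who starts below 1 cannot fall by 1 unit, and one who starts high can do so with a modest relative change. The article gives no HOMA-IR distribution, so the following is assumed: log-normal, median 2 to 3, log-SD 0.5 to 0.6, baseline to week-12 correlation 0.6 to 0.8. With three arms at the plan's 30/15/10%, logistic regression on arm and log baseline was compared with the unadjusted test.

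| Analysed per arm | Basis | Gain in power |
|---|---|---|
| 81 | all randomized, as the plan states | roughly 7 to 10 points |
| 65 | 20% dropout, completers only | roughly 10 to 15 points |

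A repeat at the corners of the assumed ranges showed a gain in every case, of about this order.

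**The case against.** The best defence is that the mismatch is one of wording. Kruskal-Wallis on yes/no data is, to within a factor of 242/243, the 2-df test that the trial was sized for, so the analysis would reach the same decision. That stands.

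A reader might infer more than the text supports in five ways:

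- **That the stated tests inflate false positives.** They do not; see the simulated error rates. The planned rates do imply unequal variances (0.3×0.7 = 0.21, 0.15×0.85 = 0.1275, 0.1×0.9 = 0.09), but under the null hypothesis they are equal, and allocation is 1:1:1.
- **That no intervals are planned.** The section promises 95% intervals. The fair criticism is that no effect measure is named for the primary outcome. A difference in 0/1 means from ANOVA is arithmetically a risk difference, but the article does not say so. An interval based on the pooled variance (0.4275/3 = 0.1425) would be about 14% too wide for low dose v placebo: √(0.285/0.2175) = 1.145.
- **That omitting covariates is itself an error.** An unadjusted comparison of randomized proportions is valid, and adjustment could properly be set in an analysis plan. It is raised here because the sentence has to be rewritten anyway.
- **That the gain in power is larger.** Two-arm scenarios with 65 per arm and 23 to 27% responders give 13 to 21 points, but those are not the plan's inputs.
- **That a shortfall in the stated power makes this worse.** The sample-size arithmetic is a separate question.

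**Conclusion.** The concern holds in this form. The article states between-group methods that do not suit its own primary endpoint and places chi-square where responder status cannot be tested, and no other section corrects this. The effect on the p-value is negligible. The real losses are two: no stated risk difference or odds ratio for each dose against placebo, and a forgone gain of roughly 7 to 10 points of power with 81 analysed per arm (10 to 15 with 65).

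The first loss follows from the text alone. The second rests on the plan's 30/15/10% rates and on an assumed HOMA-IR distribution and correlation, so its size is indicative. It should be fixed, but the validity of the trial's overall test does not depend on it.

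**What to change.** In the Statistical analysis section:

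1. State that the primary outcome is compared between groups by logistic regression on arm and baseline log HOMA-IR, with centre as an optional further term.
2. Report risk differences and odds ratios with 95% confidence intervals for each dose against placebo. Say whether the risk differences are standardised over the baseline distribution or unadjusted, because an adjusted odds ratio and a crude one are different quantities.
3. Name the 3x2 Pearson chi-square as the unadjusted check.
4. Keep ANOVA and Kruskal-Wallis for continuous outcomes, and remove chi-square from the within-group sentence.

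The cost is one paragraph. No new data are needed, and the named software fits the model; standardised risk differences take a short extra step. The Trial status section says the data were locked in June 2019, and the article does not say whether treatment codes have been opened. The change should therefore be dated before the first of the two planned unblinding steps or, if that has passed, reported openly as a later change.
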